Based on the MAAS-Global-D, we designed a multiple-component intervention, which, in brief, includes:Communication training for PCPs with interactive elements: the programme will be suitable for PCPs with professional experience. After the training sessions, the PCPs submit videos displaying their own communication with patients and receive feedback on it.Further information material for PCPs: they will be educated in the usage of Evidence-based Medicine – Guidelines (EbMG), a point-of-care tool, which will be made available online to one of the intervention groups during the whole study period and which aims to support and facilitate decision-making [23].

The groups compared will be:Group A:Intervention group A with communication trainingGroup B:Intervention group B, same training as group A plus access to EbMGGroup C:Control group C with no intervention 

By assessing and evaluating the communication training, it can be adapted and possibly also improved. Since the MAAS-Global-D instrument, as well as the associated manual, are published for free download, they will be available in order to establish nationwide training to decrease antibiotic prescribing in primary care and could be implemented in specialty training for PCPs later on.

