## Methods/Design

### Trial design

The trial is designed as a randomised, controlled trial postulating superiority of the interventions over conventional care in family practices. The study consists of three arms and a primary endpoint of antibiotic prescribing rates of PCPs for acute bronchitis, sinusitis and pharyngitis over a 3-month period starting around 1 month after the communication training and education in the usage of EbMG. Randomisation of either of the two intervention groups or the control group will be performed at practice level with a 1:1:1 allocation. Therefore, random permuted blocks will be generated. Due to the data format, practices with more than one physician represent one case. The person assigning the participants to the groups will do so blinded. Further blinding does not fit the trial design.

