### Study setting

The trial will be conducted in the population of PCPs in SH. In total, there are about 1900 PCPs in SH who are working in family practices, including rural as well as urban sites. In Germany, all resident PCPs belong to a subdivision of the Association of Statutory Health Insurance Physicians (KV). These subdivisions are responsible for the remuneration of physicians’ services when treating patients who are covered by statutory health insurance – approximately 87 % of all inhabitants [24]. Since 2011, all practices belonging to KV are obligated to do their accounting online, which requires a connection to the data centre of their KV. These routine data of the KV of Schleswig-Holstein (KVSH) will be the data basis for the present study concerning data about diagnoses. Information about prescriptions are obtained through a more complex process including pharmacies and the Central Research Institute of Ambulatory Health Care in Germany (ZI), but will also be provided by a federal subdivision of the KV together with data about diagnoses. Therefore, all data is referred to as ‘routine data’ in this article. For our objectives it is necessary to establish a connection between the PCPs and their data on diagnoses and antibiotic prescriptions. Each practice possesses an identification number, which can be used for this purpose. The study centre is located at the Institute of Family Medicine at the University Hospital of Luebeck (UKSH), SH. It will work in close collaboration with a KVSH data manager for the purpose of data analysis. Prior to analysis, official approval from the ‘Independent Regional Centre for Data Protection’ (Unabhaengiges Landeszentrum fuer Datenschutz) of the federal state of SH is sought.

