### Outcomes

#### Primary outcome measures

Evaluation of the antibiotic prescribing rate in both intervention groups compared to the control group between baseline (meaning the prescribing rate of the three periods April–June 2013, 2014, and 2015) and post-intervention (April–June 2016)

To determine the antibiotic prescribing rate for each PCP, all patients with the target-diagnoses of acute bronchitis, sinusitis and pharyngitis (classified by the *International Classification of Diseases*, *version 10* (ICD-10) codes: J01.-; J02.-; J20.- [26]) are identified in the routine data of KVSH and the proportion of these patients who receive antibiotic prescriptions is calculated. The three diagnoses and corresponding antibiotic prescriptions are condensed into one rate for each PCP (in %). This will be completed for two time periods (*t*_0_ = baseline, before intervention: mean of quarter II in the years 2013–2015; *t*_1_ = post-intervention: quarter II in the year 2016). For each PCP the change from *t*_0_ to *t*_1_ will be calculated (rate *t*_1_-rate *t*_0_). For each study group, the mean of the antibiotic prescribing rates of all PCPs in the group (at *t*_0_ and *t*_1_) will be calculated. For our primary endpoint the two intervention groups will be regarded as one group which is compared to group C.

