#### Secondary outcomes measures

Evaluation of antibiotic prescribing rate in intervention group A versus intervention group B between *t*_0_ and *t*_1_

The antibiotic prescribing rates calculated for the primary outcome will also be used for the analysis of the secondary outcomes, i.e. the mean of change in the antibiotic prescribing rate from *t*_0_ to *t*_1_. Study groups A and B will be compared to assess whether there is an additional effect in study group B due to using EbMG.Evaluation of antibiotic prescribing rates depending on PCPs’ communication skills

PCPs’ communication skills will be defined over their MAAS-Global-D score, which is computed by rating the PCPs’ videos with the MAAS-Global-D instrument. For this only the PCPs of the intervention groups are considered. For each PCP a mean score is calculated based on the six videos recorded during *t*_1_.

To evaluate the association between the MAAS-Global-D score and the antibiotic prescribing rate during *t*_1_, a linear regression will be calculated with each PCP’s antibiotic prescribing rate at *t*_1_ as dependent variable. Independent variables to be included in the model are the MAAS-Global-D score, the antibiotic prescribing rate at *t*_0_ and the difference between the two rates, the PCP’s field of specialisation, their kind of practice (single versus shared) and its location (urban versus rural) as well as the number of patients per quarter.To evaluate the communication training as well as the use and the usefulness of the EbMG by interviewing the PCPs

This process evaluation will be undertaken after *t*_1_ in terms of a qualitative, guided interview. As it is unlikely that all PCPs shall be willing to participate in the qualitative interview, additionally every participant is asked to fill in a semi-structured questionnaire with open and closed questions. The topics of both interviews will concern whether and in what way the communication training was helpful, which elements of it the PCPs used, further enablers and barriers to implementing our communication recommendations as well as additional feedback about the communication training.

A participant timeline along with the outcomes is provided in detail in the flow diagram in Fig. 1.

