### Strengths and limitations of the study

The randomisation will ensure a random distribution of characteristics and probably create nearly equal groups. Due to the number of participants, a prior stratification would not be reasonable. A limitation of the study is that randomisation must be carried out at practice level because the routine data cannot be assigned to the individual PCP in group practices. Therefore, untrained PCPs in group practices might bias the effect of the intervention.

Using the PCPs’ routine data instead of self-documentation bears the advantage that the data is not subject to selection bias: for example, if a PCP does not include all cases with the defined diagnoses in their documentation or if patients deny being in the study. Also, recall bias or effects due to the interviewer can be excluded. The Hawthorne effect is probably smaller, too, as the PCPs’ attention is not constantly drawn to patients with the relevant diagnoses. The routine data further allows the possibility of including several years as *t*_*0*_, which can balance extremes due to different seasonal variations. Extremes in *t*_1_ cannot be balanced, but a rise in antibiotic prescriptions due to a growth in infections in this time period would equally affect intervention and control groups.

Routine data is, at the same time, secondary data with known limitations: an often poorer data quality caused, for example, by misclassifications goes along with no possibility of external validation (e.g. of diagnoses) in our subsample. Further weaknesses are the lack of information on prescriptions that were not redeemed and using data covering only those patients who have statutory health insurance. Due to the data format, we do not have any further information about the ongoing of a patient’s disease, e.g. whether patients who did not use antibiotics suffer from complications afterwards. Information about side effects of antibiotics is also not available. However, these important issues will be part of the process evaluation.

Sample size calculation for this study was difficult because not only the effect size but also the *t*_0_ prescribing rate of antibiotics for the three diagnoses in Germany are based on estimates. Additionally, as in many trials, we will also be confronted with the self-selection bias of PCPs. Those interested or already sensitised for the issues (antibiotic prescription, communication skills) are more likely to participate in our study.

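### The communication-skills regression pairs one physician's MAAS-Global-D score with a prescribing rate that, in shared practices, exists only for the whole practice, so the slope is diluted there

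*Protocol article*

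**What the plan says.** **The predictor belongs to one physician.** Under Secondary outcomes measures: "For each PCP a mean score is calculated based on the six videos recorded during" t1. The Background describes the source of the score: "the PCPs submit videos displaying their own communication with patients and receive feedback on it".

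**The outcome is worded as if it also belonged to one physician.** The same section states that "a linear regression will be calculated with each PCP"'s rate at t1 as the dependent variable. Covariates include the t0 rate, the difference between the two rates, and "their kind of practice (single versus shared"). Primary outcome measures likewise speaks of a single rate per physician.

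**The data are held per practice.**
- Trial design: "Due to the data format, practices with more than one physician represent one case".
- Study setting, on linking physicians to diagnoses and prescriptions: "Each practice possesses an identification number, which can be used for this purpose".
- Strengths and limitations: "the routine data cannot be assigned to the individual PCP in group practices".

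**Shared practices are included.** Eligibility criteria admit group practices if every physician in them consents. Strengths and limitations expects that some physicians in group practices will be untrained, and names this as a possible bias in the intervention effect. It does not mention the skills regression.

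**The concern.** For a single-handed practice, score and rate describe the same doctor. For a shared practice, the score describes one doctor and the rate describes everyone in the practice. The article gives no rule for matching the two: it does not say that all partners are filmed, that their scores are averaged, or which partner's score stands for the practice. The physician-level analysis it states therefore cannot be delivered for shared practices.

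Whether better communicators prescribe fewer antibiotics is a named secondary objective. If colleagues' prescribing is mixed into the outcome, the estimated slope moves towards zero, and a weak or null result could be read as evidence that skill does not matter. A single-versus-shared indicator shifts the average level of the rate between practice types. It does not restore a slope that is flatter in one of them.

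**Working it through.** **No plan figure to reproduce for this analysis.** The article states no sample size or power for the skills regression. Its only sample size, 28 per arm, is for A+B versus C. That figure reproduces: difference 12, SDs 15.6 and 19.2, two-sided 5 %, Satterthwaite t test with 56 versus 28 gives power 0.801. This point does not touch it.

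**Step 1: slope within a shared practice.** Assume:
- k doctors with equal case load, so the practice rate is the mean of their k rates;
- each doctor's rate depends on his or her own score with slope β;
- scores have equal variance and correlate at ρ between colleagues;
- one doctor is scored, and there are no other covariates.

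The expected slope of the practice rate on that doctor's score is then

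β × (1 + (k−1)ρ) / k.

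| k | ρ=0 | ρ=0.5 | ρ=1 |
|---|---|---|---|
| 2 | 0.50 | 0.75 | 1.00 |
| 3 | 0.33 | 0.67 | 1.00 |

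The article gives neither k nor ρ; both are assumed.

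**Step 2: slope over all practices.** If a share s of the rows comes from shared practices, the pooled slope is about β × [(1−s) + s(1+(k−1)ρ)/k]. With an assumed β of −0.40 on standardised scales:
- s=0.5, k=2, ρ=0: −0.40 × (0.5 + 0.5×0.50) = −0.30
- s=0.5, k=3, ρ=0: −0.40 × (0.5 + 0.5×0.333) = −0.27
- s=0.7, k=3, ρ=0: −0.40 × (0.3 + 0.7×0.333) = −0.21
- s=0.7, k=3, ρ=0.5: −0.40 × (0.3 + 0.7×0.667) = −0.31

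Simulation with 56 scored physicians (28 × 2 arms, an assumption) gives −0.31, −0.27, −0.22 and −0.31. Power is about 0.87 with no shared practices. At ρ=0 it falls to 0.76 (s=0.5, k=2), 0.71 (s=0.5, k=3) and 0.60 (s=0.7, k=3). At ρ=0.5 it stays between 0.87 and 0.89, although the slope is still too flat.

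**Step 3: effect of averaging scores.** If j of the k doctors are filmed and their scores averaged, the factor becomes [(1+(k−1)ρ)/k] ÷ [(1+(j−1)ρ)/j]. For j=k it is 1, so the dilution disappears. For j=2, k=3 it is (1/3)÷(1/2) = 0.67 at ρ=0 and (2/3)÷(0.75) = 0.89 at ρ=0.5. Averaging helps, and removes the problem fully only where every partner is filmed.

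**Step 4: the model as listed.** Primary outcome measures defines the change as rate t1 minus rate t0. The covariates include the t0 rate and the difference between the two rates, so

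rate t1 = 1 × rate t0 + 1 × (rate t1 − rate t0).

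The fit is perfect and the score coefficient is zero whatever the data. A check on simulated data gave coefficients of 1 and 1 for these two terms, 0 for the score, and no residual. Steps 1 to 3 therefore describe a model from which the difference has been removed.

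**The case against.** **The model as written has no slope to dilute.** This is true, and it is the more basic defect in the same sentence. It does not make the unit mismatch harmless: once the difference is dropped, as it must be, the mismatch remains.

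**Colleagues influence each other, so ρ=0 is a worst case.** This is fair. The eligibility criteria expect a trained physician to influence colleagues. At ρ=0.5 power hardly changes, but the slope still understates the physician-level association.

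**A journal article may leave aggregation to the analysis plan.** This stands in part. A detailed matching rule could appear there. But the article does not leave the unit open: it names a physician-level rate that its own data description says is unavailable in group practices. The limitation it discloses is tied to the intervention effect only.

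**Two stronger readings are tempting and not supported.**
- A reader might infer that score and outcome belong to different doctors. They overlap, because the practice rate includes the filmed doctor's own cases.
- A reader might infer that partners would be entered as several rows with the same rate, so that standard errors are too small by √k. Trial design speaks against this by counting a multi-physician practice as one case. √k is also only the limit for identical partner scores: in a simulation with duplicated rates and no true slope, the true-to-reported standard error ratio was about 1.0 at ρ=0 (k=2 or 3) and reached 1.48 and 1.77 only at ρ=1. At ρ=1 there is no dilution, so the two effects are not both at their worst together.

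**Restricting the main analysis to single-handed practices could do more harm than the dilution.** This stands. With half the practices shared, 28 rows remain and power for a correlation of −0.40 is about 0.57, against 0.76 or 0.71 for the diluted analysis of all 56 at ρ=0.

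**Conclusion.** The point holds for shared practices. The regression joins a physician-level score to a practice-level rate, and the practice-type main effect does not repair this. Within shared practices the slope is multiplied by roughly 0.33 to 0.75 for k of 2 or 3 and ρ from 0 to 0.5. In the mixed-sample examples above, the overall slope falls from −0.40 to between −0.21 and −0.31. These sizes rest on assumed k, ρ, share of shared practices and true correlation, on equal case loads, and on a model without other covariates; the actual dilution cannot be computed from the article. Single-handed practices are not affected, and neither is the primary comparison, where practices are randomised. The matter should be settled before analysis because it bears on a stated secondary objective, but that objective is exploratory.

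**What to change.** In Secondary outcomes measures and in the Analysis section:

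1. Define the practice as the unit of the skills regression, with one row per practice, in line with Trial design.
2. Use the mean MAAS-Global-D score of all filmed physicians in the practice, and report how many of its physicians were filmed.
3. Add a score-by-practice-type term, so that the slope may differ between single and shared practices.
4. Report single-handed practices, where score and rate match, as a sensitivity analysis and not as the main one.
5. Remove the difference between the t1 and t0 rates from the covariates and keep the t0 rate.
6. Interpret the all-practice slope as a practice-level association, and extend the stated limitation on group practices to this analysis.

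No new data are needed. The cost is a slightly more complex exploratory model and low precision in the single-handed subset. Some dilution remains wherever not all partners were filmed.

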##### Secondary outcomes

The additional effect of the EbMG will be evaluated similarly to the primary outcome under consideration of group A versus group B. Since the sample size is calculated with regard to the primary outcome, these analyses are only exploratory.

For further secondary outcomes, PCPs who adhered to the protocol will be encompassed in the analyses. Adherence refers to the intervention groups and whether each PCP has submitted a minimum of at least four videos. To explore differences in the antibiotic prescribing rate at *t*_1_ depending on the communication skills of the PCPs in group A and B, linear regression analyses will be conducted.

Quantitative data from the evaluation questionnaire will be presented descriptively only.

For all analyses, 95 % confidence intervals will be calculated where applicable.

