## Discussion

The MAAS-Global-D instrument, which measures communicative and medical skills, has recently been translated into German [22] and will be tested in a randomised controlled trial in primary care in Germany for the first time. The trial design (three arms: multiple interventional elements and comparison with a control group) contributes to an insight into the effectiveness of the different components to reduce antibiotic prescribing, which will also be supported by extensive evaluation. Thereby, barriers and enablers to implement parts of or the whole of the communication training on a large scale will be worked out. The choice of active clinician education procedures and further educational material for the PCP, such as EbMG, would appear to be promising intervention strategies [15, 16].

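### The MAAS-Global-D regression omits randomised arm, and its covariates fix the outcome; once that is repaired, an EbMG effect could partly be read as communication skill

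*Protocol article*

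**What the plan says.** The protocol article, under Secondary outcomes measures, defines the model: "a linear regression will be calculated with each PCP’s antibiotic prescribing rate at" t1 as dependent variable. On the sample it says "For this only the PCPs of the intervention groups are considered". The covariates are listed by name. The list opens "Independent variables to be included in the model are the MAAS-Global-D score", adds the rate at t0, and continues "and the difference between the two rates, the PCP’s field of specialisation, their kind of practice (single versus shared) and its location", ending with the number of patients per quarter. Neither study arm nor EbMG access is in it.

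The Analysis section (Secondary outcomes) repeats the pooling: differences in the t1 rate are explored "depending on the communication skills of the PCPs in group A and B, linear regression analyses will be conducted". It limits the sample by adherence, defined as "whether each PCP has submitted a minimum of at least four videos".

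Three other statements bear on the point:

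- **What separates the arms.** Under Interventions, both arms get the same communication training. Arm B alone also gets 1.5 hours of EbMG teaching and online access. A further fall in prescribing in B is a secondary objective.
- **What the score contains.** The Discussion describes it as follows: "The MAAS-Global-D instrument, which measures communicative and medical skills". The Secondary objectives and the outcome section read a higher score as better communication skill.
- **What the difference is.** Under Primary outcome measures, the sentence beginning "For each PCP the change from" defines it as the t1 rate minus the t0 rate.

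**The concern.** The covariate list goes down to practice location but omits the one factor that the trial randomised within this sample. By the protocol's own objectives, arm may affect the outcome. The score is not purely a communication measure, so a guideline tool could plausibly affect it too. If both links hold, arm is a common cause of score and prescribing, and an unadjusted slope mixes the association of interest with the effect of EbMG.

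The same sentence has a prior problem. With the t0 rate and the difference both on the right-hand side, the outcome is reproduced exactly and the score has nothing left to explain. Any remedy has to deal with that first.

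At stake is the answer to the second secondary objective, whether physicians with higher scores prescribe fewer antibiotics.

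**Working it through.** **1. Size of the regression sample.** The article gives no figure for the regression, so I start from its sample size. The inputs are changes of -4 (SD 15.6) and +8 (SD 19.2), 80 % power, alpha 5 % (taken as two-sided) and 1:1:1 allocation, so A+B versus C is 2:1. The Satterthwaite t test gives power 0.801 with 28 per arm and 0.786 with 27, so the stated 28 reproduces. Then 3 × 28 = 84, and 84 × 1.1 = 92.4, rounded up to 93, or 31 per arm. Arms A and B together hold 2 × 31 = 62 physicians, or 2 × 28 = 56 after the planned dropout. The four-video rule can reduce this further.

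**2. The model as listed.** Write R0 and R1 for the two rates, S for the score and D = R1 − R0. Then

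R1 = 0 + 0·S + 1·R0 + 1·D + 0·(all other covariates)

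holds exactly for every physician. Least squares finds this solution with zero residual. In simulated data the largest residual was about 1e-13 and the score coefficient about 1e-14 at every EbMG effect tried. An arm term would also receive coefficient 0 and change nothing.

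**3. The model without D and without arm.** Let Z = 1 in arm B and 0 in arm A, in equal numbers, so Var(Z) = 0.25. Let EbMG shift the score by d (in within-arm SDs) and the t1 rate by g percentage points, with no true score effect. The expected slope per within-arm SD is

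Cov(S, gZ) / Var(S) = 0.25·g·d / (1 + 0.25·d²).

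- d = 0.5, g = -5: -0.625 / 1.0625 = -0.59
- d = 1, g = -10: -2.5 / 1.25 = -2.0

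The documents give neither g nor d, so both were varied. The simulation used 3,000 runs per setting, n = 56, residual SD 15.6 and the other listed covariates in the model. The t0 rate was drawn with mean 31 and an assumed SD of 15.

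| g (points) | d (SD) | Formula | Slope, no arm term | False positives, no arm term | Slope, arm term | False positives, arm term |
|---|---|---|---|---|---|---|
| -3 | 0.25 | -0.19 | -0.19 | 5.0 % | -0.01 | 5.3 % |
| -5 | 0.5 | -0.59 | -0.62 | 5.3 % | -0.02 | 4.5 % |
| -5 | 1 | -1.00 | -0.97 | 6.7 % | 0.00 | 4.6 % |
| -10 | 0.5 | -1.18 | -1.18 | 7.1 % | 0.01 | 4.3 % |
| -10 | 1 | -2.00 | -2.12 | 18.2 % | -0.08 | 5.9 % |

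With n = 62 the picture is the same. For example, g = -10 and d = 1 gives a slope of -2.07 and 17.7 % false positives without an arm term, against -0.06 and 4.9 % with it.

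**4. If EbMG does not move the score (d = 0).** The formula gives 0. Omitting arm then only adds 0.25·g² to the residual variance. For g = -5 the residual SD rises from 15.6 to √(243.36 + 6.25) = 15.8. For g = -10 it rises to √(243.36 + 25) = 16.4.

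**The case against.** The strongest reply is that the harm cannot occur in the model the article states. A reader who sees the missing arm term might infer that the planned regression could return a negative slope produced wholly by EbMG. The documents do not support that: with the t0 rate and the difference both included, the score coefficient is 0 whatever EbMG does. Adding arm alone would leave the regression just as uninformative. This stands. The slopes in the table belong to a repaired model that the article does not state.

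The link from EbMG to the score is also conjecture. No section says that EbMG raises it. Both arms receive the same communication training, the physicians choose their own videos, and the filmed consultations need not concern respiratory infections. This stands as well. The link is plausible only because the instrument also covers medical skills and EbMG is described as a general decision aid with patient information.

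The bias is also small for moderate inputs. The standard error of the slope is about 15.6/√56 = 2.1 points per SD, so -0.6 is under 0.3 standard errors. Only the most extreme pair raises false positives markedly, and it credits EbMG alone with roughly the 10–12 % absolute reduction that the Background reports from earlier communication-training studies.

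What the reply does not remove is that the difference has to go if the regression is to answer its objective. The model left behind then pools two randomised arms with no term for arm.

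**Conclusion.** The point holds in a limited form. The listed covariates determine the outcome and omit randomised arm. The first defect makes the score coefficient 0 and is the more serious for this analysis. The second takes effect only once the first is repaired.

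In the repaired model, part of an EbMG effect would be read as a communication-skill association if EbMG both lowers prescribing and raises the score. The assumed ranges (g from -3 to -10 points, d from 0.25 to 1 SD) give a spurious slope of about -0.2 to -2 points per SD. The false-positive rate stays at about 5–7 % in the pairs tabulated, except 18 % at the extreme one. If EbMG does not shift the score, there is no bias and a small loss of precision.

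The article presents this regression as exploring an association in a secondary analysis. The primary comparison of A+B with C is not affected.

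**What to change.** Make two changes together in the model under Secondary outcomes measures:

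1. Remove the difference between the two rates from the independent variables, keeping the t0 rate.
2. Add randomised arm (A or B) as a covariate, so that the score coefficient compares physicians within the same arm. Carry the same wording into the Analysis section.

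The arm term costs 1 degree of freedom among at most 62 physicians, and removing the difference gives one back. No new data are needed.

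A sensitivity analysis with a score from the communication items alone would also help, but only if those items can be separated from the medical ones. The documents do not describe the item structure, so this is conditional.

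### The regression of the t1 prescribing rate on the MAAS-Global-D score also adjusts for the t0 rate and for the t1 − t0 change, so the score's coefficient is zero whatever the data show

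*Protocol article*

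**What the plan says.** The second secondary objective asks whether physicians with higher MAAS-Global-D scores prescribe antibiotics less often. The model is set out in the protocol article under Secondary outcomes measures, with the aim "To evaluate the association between the MAAS-Global-D score and the antibiotic prescribing rate during" t1.

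- **Outcome:** "a linear regression will be calculated with each PCP’s antibiotic prescribing rate at *t*_1_ as dependent variable".
- **Covariates:** "Independent variables to be included in the model are the MAAS-Global-D score, the antibiotic prescribing rate at *t*_0", followed directly by "and the difference between the two rates", and then specialty, type of practice, urban or rural site, and patient volume.
- **Definition of the difference** (Primary outcome measures): "For each PCP the change from *t*_0_ to *t*_1_ will be calculated (rate *t*_1_-rate *t*_0".
- **Link between the sections** (Secondary outcomes measures): "The antibiotic prescribing rates calculated for the primary outcome will also be used for the analysis of the secondary outcomes".

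The Analysis section returns to this objective only briefly under Secondary outcomes: "depending on the communication skills of the PCPs in group A and B, linear regression analyses will be conducted". It adds that physicians must have submitted at least four videos, and gives no further covariate list.

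**The concern.** The only two rates in that paragraph are the t0 and t1 rates, so the difference used as a covariate is built from the outcome. Together with the t0 rate it reproduces the outcome exactly, and nothing is left for communication skill to explain.

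Two things are at stake. The printed result would be a score coefficient of zero, which a reader could take as evidence that communication skill is unrelated to prescribing. More likely, the analysts would notice the perfect fit and pick a replacement model after seeing the data, which loses the benefit of having specified the model in advance.

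**Working it through.** **The plan's own figures.** The article gives no numerical result for this regression. Its only computed figure is the sample size for the primary comparison: 28 per arm, or 31 with dropout. It reproduces: a two-sided 5 % Satterthwaite t test of A+B against C (2:1), with a difference of 12 points and SDs of 15.6 and 19.2, has power 0.801 at 28 per arm. It matters here only because it limits the regression to groups A and B with 2 × 28 = 56 to 2 × 31 = 62 physicians, fewer once the four-video rule is applied.

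**Step 1: algebra.** Write y0 and y1 for a physician's rates at t0 and t1, d = y1 − y0, and M for the MAAS-Global-D score. The specified model is

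y1 = b0 + b1·M + b2·y0 + b3·d + (four practice covariates) + error.

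For every physician, y1 = y0 + (y1 − y0) = 1·y0 + 1·d. Setting b2 = b3 = 1 and all other coefficients to 0 makes every residual zero. No fit can have a smaller residual sum of squares, so this is the least-squares solution. It is unique when the design matrix has full rank, and then b1 = 0 whatever the true association.

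**Step 2: numerical check.** Ordinary least squares was run with an intercept and all seven listed covariates (eight parameters) on 2,000 simulated data sets at each of n = 56 and n = 62. The inputs are assumptions, not figures from the article:

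- y0: mean 40, SD 15
- M: mean 3, SD 0.6
- y1 = y0 − 4 − 8·(M − 3) + error, error SD 14

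| | n = 56 | n = 62 |
|---|---|---|
| Largest absolute score coefficient, model as written | 3.4e-14 | 2.8e-14 |
| R², model as written | 1 | 1 |
| Rank of design matrix (of 8) | 8 | 8 |
| Mean score coefficient, change removed | −8.0 | −8.1 |
| Runs with p < 0.05, change removed | 66 % | 73 % |

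Because the matrix has full rank, software has no exact collinearity to report. In the first run at n = 62, the printed score coefficient was 5.3e-15 with standard error 6.6e-15, a ratio of 5.3/6.6 ≈ 0.8. That would look like an ordinary non-significant result, but both numbers are rounding noise.

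**Step 3: would dropping y0 instead of d help?** No. Since y1 − d = y0, the score coefficient from regressing y1 on M and d equals the one from regressing y0 on M and d. It describes the baseline rate, not the t1 rate. In a simulation with M and d only (n = 62, same assumptions), its mean was 0.0006 despite the true slope of −8.

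**Step 4: would a slightly different t0 in the two terms rescue it?** The article defines only one t0. If the two versions nevertheless differed with SD 1 point (an assumption), the mean score coefficient was −0.002 (SD 0.23), still nowhere near −8.

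**Step 5: the change as outcome.** Subtracting y0 from both sides of the corrected model lowers the coefficient of y0 by 1 and leaves the rest alone. In the first run at n = 62, the score coefficient was −6.99 (SE 3.19) with either outcome.

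**The case against.** The strongest points on the other side concern scope and reading rather than the algebra.

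- **It is one secondary analysis**, in groups A and B only and introduced as exploratory in purpose. This stands. The t test of A+B against C and the sample size are untouched.
- **Separate models may have been meant.** The Analysis section speaks of regression analyses in the plural. That is possible, but the section that lists the covariates says "a linear regression will be calculated with each PCP" and refers to one model, with the two terms joined as members of one list. The plural neither removes the change nor describes alternatives, and Step 3 shows that a t1 model with the change but without the t0 rate would not work either.
- **A separate analysis plan may put it right.** An article may leave detail to another document, but here it states an outcome and a covariate list, and that statement is wrong.
- **The harm is speculative**, because an R² of 1 would be noticed. This stands in part. Misreporting a zero as a finding is the less likely outcome; an unplanned change of model after seeing the data is the more likely one.
- **No data are lost.** This also stands. The objective can still be answered, only not by the model as written.

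**Conclusion.** The concern holds. As specified, the regression is an identity: coefficients of 1 on the t0 rate and on the change, R² = 1, and zero for the MAAS-Global-D score and every other covariate. It carries no information on the second secondary objective.

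This rests on the article's single definition of t0 and of the change, and on a full-rank design, which is plausible with eight parameters and up to 56 to 62 physicians. Without full rank the coefficients are not unique, but the fit is still perfect and still uninformative. It does not depend on the simulation inputs, which only illustrate it. The percentages of significant runs depend on those assumptions and say nothing about the power this trial would have.

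The model must be corrected before this analysis is run. The primary comparison needs no change on this account.

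**What to change.** Delete the difference between the two rates from the covariate list. Keep the t1 rate as outcome, with the MAAS-Global-D score, the t0 rate and the four practice characteristics as covariates. If the sponsor prefers to report change, the change can be the outcome with the t0 rate as covariate, since the score coefficient and standard error are the same. The change should not stand on the right-hand side in either form.

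The cost is one phrase in the protocol and in any analysis plan that repeats it, with no new data and no burden on physicians or patients. The correction should be dated before the t1 prescribing data are analysed, so that the model remains prespecified.
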